## Abstract

**Introduction:**

Saltwater intrusion and salinisation have contributed to drinking water scarcity in many coastal regions globally, leading to dependence on alternative sources for water supply. In southwest coastal Bangladesh, communities have few options but to drink brackish groundwater which has been associated with high blood pressure among the adult population, and pre-eclampsia and gestational hypertension among pregnant women. Managed aquifer recharge (MAR), the purposeful recharge of surface water or rainwater to aquifers to bring hydrological equilibrium, is a potential solution for salinity problem in southwest coastal Bangladesh by creating a freshwater lens within the brackish aquifer. Our study aims to evaluate whether consumption of MAR water improves human health, particularly by reducing blood pressure among communities in coastal Bangladesh.

**Methods and analysis:**

The study employs a stepped-wedge cluster-randomised controlled community trial design in 16 communities over five monthly visits. During each visit, we will collect data on participants’ source of drinking and cooking water and measure the salinity level and electrical conductivity of household stored water. At each visit, we will also measure the blood pressure of participants ≥20 years of age and pregnant women and collect urine samples for urinary sodium and protein measurements. We will use generalised linear mixed models to determine the association of access to MAR water on blood pressure of the participants.

**Ethics and dissemination:**

The study protocol has been reviewed and approved by the Institutional Review Boards of the International Centre for Diarrheal Disease Research, Bangladesh (icddr,b). Informed written consent will be taken from all the participants. This study is funded by Wellcome Trust, UK. The study findings will be disseminated to the government partners, at research conferences and in peer-reviewed journals.

**Trial registration number:**

NCT02746003; Pre-results.

Strengths and limitations of this studyThis is the first study to evaluate the health impact of managed aquifer recharge (MAR) in southwest coastal Bangladesh.The stepped-wedge trial ensures we will have counterfactual data as well as gradual access to MAR water in all communities.Objective measurement of exposure (drinking water salinity) and outcomes (urinary sodium and blood pressure).The magnitude of exposure will vary geographically and across time period. Therefore, MAR water salinity will differ across communities at a single point of time, and also for the same community at different points of time.Compliance of the intervention may be different across sites and for individuals of different socioeconomic status.

## Introduction

### Background and rationale

Saltwater intrusion and salinisation have increased groundwater salinity in many coastal aquifers and small islands across the world.^1–5^ This is driven by a number of climatological and anthropogenic factors including global warming, increased cyclones and tidal surges, reduced river discharge and increased groundwater abstraction in excess of recharge.^6–8^ Communities in many coastal regions rely on groundwater as their main source of drinking water^9^ as well as freshwater for domestic, agricultural and industrial purposes.^10^ Nearly half of the world’s population resides in coastal areas^3^ and 10% of these live in low-lying coastal areas where surface elevation is generally <10 m above mean sea level.^11^ Salinisation in coastal areas is expected to increase in the future because of increased groundwater withdrawal due to population and economic growth and sea level rise.^3^ As the world's population and economic activities continue to grow, groundwater supplies are progressively under threat of depletion, which increases the importance of monitoring, management and conservation of coastal freshwater aquifers.^12 13^

One approach to minimise the impact of groundwater salinisation is to enhance groundwater recharge into coastal aquifers.^14^ Managed aquifer recharge (MAR) is an approach to artificially promote freshwater recharge to increase storage. MAR involves infiltration of freshwater (eg, rainwater and pond water) into aquifers to create a store of freshwater within the naturally brackish aquifer (figure 1).^15–17^ MAR represents a promising adaptive strategy for increasing freshwater availability and sustaining a year-round drinking water supply that is protected from evaporation, and could be resilient to tidal storms, cyclones and surface water salinity since freshwater infiltration and storage occur under confined conditions.^18^

**Figure 1 F1:**
[figure not shown]
Schematic diagram of the managed aquifer recharge systems in southwest coastal Bangladesh.

The brackishness of groundwater in southwest coastal Bangladesh is caused by a combination of climatic and anthropogenic factors including sea level rise, frequent cyclones and tidal storms, and shrimp cultivation.^19–22^ In the future, climate change and sea level rise are expected to cause more cyclones, tidal surges and flood in this region that will further affect surface water and groundwater salinity.^7^ In many areas in southwest coastal Bangladesh, both shallow and deep aquifers contain naturally brackish water causing acute scarcity of drinking water (figure 2).^23 2 4^ Water salinity in southwest coastal Bangladesh follows a clear seasonal pattern─higher in the dry season than the wet season.^25^ Salinity of water bodies builds up from October to May, peaking during February to early May. After May, salinity decreases sharply due to rainfall and increased upstream river flow. People collect and use rainwater for drinking and cooking purposes during the monsoon when precipitation is intense, but during the dry season, they generally rely on pond water or saline tube well water.^26^

**Figure 2 F2:**
[figure not shown]
(A) Groundwater salinity (measured as EC: electrical conductivity) distribution in coastal Bangladesh (data source: Bangladesh Water Development Board) and (B) location of the 75 managed aquifer recharge sites in southwest coastal region illustrated by red dots (data source: [name] [name]).

The Geology Department of the University of Dhaka, in collaboration with Unicef, and the Department of Public Health Engineering (DPHE), Government of Bangladesh, have piloted 20 small-scale MAR projects in three districts of southwest coastal Bangladesh to evaluate the feasibility of MAR for drinking water supply in rural communities.^27^ The shallow brackish aquifer was the target storage zone that is overlain by Holocene clay aquitard of 3–15 m thickness.^16^ In the pilot phase, an average storage of approximately 900 m^3^ of freshwater per year per site was established, sufficient to deliver 15 L of safe drinking water per day per household, which can fulfil the demand for drinking and cooking for approximately 300 people in 60–70 households during the dry season.^28 29^ The second phase of the MAR project started in 2014 aiming to install 75 MAR systems in three districts of southwest coastal Bangladesh: Satkhira, Khulna and Bagerhat (figure 2B). In March 2016, thirty MAR sites were handed over to the community for water consumption. The remaining 45 sites are expected to be ready by November 2016 following infiltration of water during monsoon of 2016 (June to October 2016).

Epidemiological studies have demonstrated that high sodium intake is associated with elevated blood pressure^30–32^ and other cardiovascular diseases.^33^ A study conducted among the adult population residing in southwest coastal Bangladesh suggests drinking saline water was associated with high blood pressure after adjusting for personal, lifestyle and environmental factors.^34^ Among study participants, the mean systolic blood pressure for those consuming water with sodium from the lowest quintile was 119.4 (SD 13.7) and from the highest sodium quintile was 126.7 mm Hg (18.0).^34^ Excess sodium intake from drinking brackish water has been also associated with increased gestational hypertension and pre-eclampsia among pregnant women in southwest coastal Bangladesh.^35 36^ Mean systolic and diastolic blood pressures were higher among the pregnant women who drank tube well or pond (saline sources) water compared with those who drank rainwater.^35 37^ The mean systolic blood pressure of pregnant women from these areas was 102.4 mm Hg among those who drank rainwater, 112.6 mm Hg among pond water users and 119.4 mm Hg among brackish groundwater users.^35^ High blood pressure during pregnancy is associated with high maternal mortality, and adverse pregnancy and fetal outcomes.^38^

There are 37 million people living in the southwest coastal region and 20 million are currently affected by drinking water salinity.^39^ The estimated mean global sodium consumption is 3.95 g/day (range 2.2–5.5 g/day),^40^ but people in southwest coastal Bangladesh consume up to 16 g of sodium per day through drinking brackish groundwater.^41^ While MAR water can potentially reduce exposure to saline water, the health effects of providing access to MAR water have not been investigated. Characterising the health consequences of shifting from current drinking water supply to MAR water can assist decision makers to assess the value of scaling up MAR. Many water interventions, for example, failed to achieve health impact, because people do not use them. There is also considerable controversy on whether reducing sodium intake improves health.^42^ In addition, the MAR system will also alter the intake of other cations such as calcium and magnesium that may have health impact.^43–46^ Because the cost of these systems is high and their long-term feasibility an open question, clarifying the amount of health benefit, if any, is an important step that can help inform future efforts to provide water to communities faced with high levels of groundwater salinity. The human subject committees who reviewed the study appreciated the uncertainty in bringing solutions to scale in this setting and considered it appropriate to include health measurements of participating residents to objectively evaluate the potential impact.

### Objectives

Randomised controlled trials demonstrate that reduction in dietary sodium in adults decreases blood pressure among people both with and without hypertension.^47–49^ Meta-analysis of randomised trials also suggests modest reduction in salt intake for 4 or more weeks causes significant reduction in blood pressure at the population level.^50 51^ The primary objective of the study is to assess whether access to low-salinity MAR water can reduce blood pressure of community members ≥20 years of age. Secondary objectives include whether access to MAR water can reduce urinary sodium and total protein excretion. We will evaluate water salinity, urinary sodium excretion and blood pressure so that we understand whether or not we achieved our immediate targets along the causal pathway.

## Methods

### Study design

We will implement a stepped-wedge cluster-randomised controlled trial in 16 MAR communities. MAR system is a community-based intervention designed to supply low-salinity water for 60–70 households in a village or community. MAR intervention cannot be implemented and randomised at individual or household levels. Once a community will have access to MAR water, it is difficult to withhold the access of MAR water for some households. Therefore, we will conduct a cluster-randomised trial where each community will be considered as a cluster. The stepped-wedge design allows communities to gradually have access to MAR water; however, the point at which their access commences will be randomly assigned.^52^ In this way, each MAR site will contribute data for both the intervention and the control time periods. We will have five monthly steps in the stepped-wedge trial (figure 3). In the first step, none of the communities will have MAR water available for drinking and we will collect baseline information. During each subsequent month, four randomly selected communities will receive access to MAR water for drinking and cooking. In the last (fifth) monthly step, all the communities will have access to MAR drinking water.

**Figure 3 F3:**
[figure not shown]
Timeline of blood pressure measurement with number of managed aquifer recharge communities and participants in preintervention (blue colour) and postintervention (brown colour) time period in different steps.

### Study settings

The study will be conducted at the community level in three districts in southwest coastal Bangladesh─Khulna, Satkhira and Bagerhat─where 75 MAR systems have been installed. Of these, 30 systems are already in use. We will select 16 communities for study based on consultation with the implementers of MAR systems (Dhaka University and Unicef Bangladesh). Three criteria need to be met for inclusion of communities in the study: communities have not started drinking MAR water, acceptable level of arsenic (<50 µg/L) in drinking water set by the government of Bangladesh^53 54^ and electrical conductivity (a measure of salinity) of water below 2000 μS/cm, an indication that the MAR system has successfully reduced salinity in the aquifer.

### Participant eligibility criteria

The inclusion criteria will be household members ≥20 years old and pregnant women who willingly agree to exclusively use MAR water during the dry season for drinking and cooking purposes. The Dhaka University team have determined the catchment area for each MAR site based on geographical distance from MAR infrastructure and have developed a list of households who expressed willingness to drink MAR water. Any ≥20-year-old hypertensive household members will be also eligible for participation but research staff will collect information about their medication if any. Research staff will enrol postadolescent ≥20-year population as an individual’s response to salt intake (salt-sensitivity) increases with age^55^ and adolescence is associated with adrenal and nervous system maturation that may contribute to salt sensitivity.^56 57^ They will approach households living near the MAR water access point. They will enrol the 28 closest households surrounding each MAR system that meet the inclusion criteria and consent (online supplementary information 1) to study participation. During the informed written consent process, research staff will inform each household that they will be randomly selected when to start consuming MAR water as part of the scientific process of the study. All household members >20 years of age will be eligible and enrolled in the study from the selected 28 households. In addition, research staff will enrol households that include a pregnant woman in each selected MAR catchment community irrespective of household selection from a list of pregnant women developed by a female promoter.

10.1136/bmjopen-2016-015205.supp1Supplementary file 1

### Randomisation and intervention delivery

We will randomly select four MAR communities to drink MAR water in each step following the first (baseline) step (figure 3) by computer-generated random numbers. Randomisation will be conducted by an investigator who will not be directly involved in implementation of the stepped-wedge study and this will be done before commencement of the study. The study could not be blinded, therefore there was no concealment from the cluster participants. Although infiltration of rainwater and pond water into the brackish aquifer through the MAR systems will be ongoing for 1–2 years in each community, people will not have access to MAR water until a formal handover of MAR systems to community members. The implementers hire a caretaker or gatekeeper for each MAR community who is responsible for maintenance of the respective MAR system prior to the community handover. The implementers form a community management team who are responsible for maintenance of each MAR system following handover. We have synchronised the community handover with the randomisation schedule in the 16 communities after consulting with the gatekeepers. Community health promoters will inform the participants when the MAR water will be available for consumption once the community management team is formed. Agreement of the implementers and gatekeepers was sought at the beginning of the study during site selection for inclusion of any site in trial and access of MAR water as per the randomisation.

We will deploy a local trained promoter at each MAR site, who will visit these households, list members and identify pregnant women in these and other households in catchment areas of each MAR site. Promoters will encourage all household members to drink MAR water exclusively while they are at home, carry a bottle of MAR water while they go out for work and other activities, and to cook with MAR water. The community health promoters will visit households with promotional materials (eg, flip charts) from the beginning of the study to inform household members about adverse health effects of drinking brackish water and potential benefits of drinking low-salinity MAR water. As per the randomisation schedule, they will inform households when MAR water will be available for consumption.

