### Sample size

The sample size of the stepped-wedge trial was calculated based on the effect of MAR systems to reduce systolic blood pressure of the ≥20-year-old community members. Data from southwest coastal Bangladesh demonstrated a 7 mm Hg lower mean systolic blood pressure among pregnant women who drank pond water compared with those who drank brackish water, and a 17 mm Hg lower mean systolic blood pressure for pregnant women who drank rainwater compared with those who drank brackish water.^35^ The mean reduction in systolic blood pressure following long-term modest salt reduction is 4.2 mm Hg.^50^ For calculations, we considered a mean systolic blood pressure reduction of at least 3 mm Hg among the communities who will have access to MAR water for drinking and cooking purposes compared with those who will use brackish water. The entire population under the MAR community catchment area will be considered as one cluster. Each MAR community serves approximately 300 people, constituting 60–70 households in the catchment area.^28^ The mean household size in southwest coastal Bangladesh is 4.2, approximately 52% of household members are ≥20 years old.^58 59^ Since we will collect blood pressure from all household members ≥20 years old, we estimated an average of 2.2 participants in this age group per household. We will select 28 households per cluster (28×2.2=60 people per cluster). A previously published study in Bangladesh reported SD 13.51 for systolic blood pressure,^60^ but we considered SD 20 for systolic blood pressure to capture a greater variation of blood pressure. We calculated the sample size for the stepped-wedge trial adopting the formula used by Hussey and Hughes.^61^ Although their formula assumed no within-participant correlation over time (cross-sectional design), we applied their formula for a cohort design (same participant followed up over time). The salinity problem and the MAR water quality may be influenced by seasonality over the progression of dry season and participants’ blood pressure may respond differently to different level of sodium exposure in MAR drinking water. Therefore, it is important that we investigate the effect of the MAR system on the same participants over the entire dry season. Since we will investigate the same participants in each step, we will have less participant-level variability and sufficient power compared with a cross-sectional design to investigate the effect of MAR systems. We initially calculated the sample size for a simple unadjusted trial (N_U_), and then multiplied by the design effect for a stepped-wedge trial (DE_SW_). The sample size for a simple unadjusted trial was calculated as 1396 participants (effect size=3, SD of 20 for both groups, 80% power and 5% type I error). The DE_SW_ was 3.04 based on a formula provided by Hussy and Hughes, therefore sample size was 1396×3.04. We also inflated the total sample size considering 10% loss to follow-up. We then followed the approaches of determining the number of clusters required for total sample size considering a fixed cluster size of 60.^62^ We then calculated the number of steps that we need to randomise by dividing the total cluster by steps. We calculated that 16 MAR communities will be required for the study with four communities randomised to access MAR water in each step (figure 3).

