## Discussion

This will be the first study to assess the health impact of an environmental intervention to reduce groundwater salinity in southwest coastal Bangladesh. Our study has several strengths. The stepped-wedge trial ensures that we will have counterfactual data as well as gradual access to MAR water in all communities. In a stepped-wedge design, treatment effect of an intervention can be estimated from between and within-cluster comparisons as participants will act as their own control, compared with only between-cluster comparison in a parallel cluster-randomised design.^61^

We explored other study designs such as non-randomised study. As per suggestion of icddr,b’s Ethical Review Committee, we conducted a pilot study in four communities (two MAR communities and two non-MAR communities) from May to August 2016. Pilot study findings suggested that because of the heterogeneity in village-level hydrogeological conditions and in participation by community residents with different characteristics, non-randomised quasiexperimental studies would be expected to generate unequal distribution of confounders that would undermine scientific inference. The objective of the pilot study was to pretest our data collection instrument laboratory protocols prior commencement of the main study. We identified unequal distributions of several important observed confounders across the communities such as socioeconomic status, and household characteristics such as supply of electricity and ownership refrigerator. We identified that some covariates such as supply of electricity were perfectly predictive of communities receiving MAR interventions. We were unable to derive satisfactory matching of MAR intervention and control households after principal component analysis. The findings highlighted the importance of a randomised trial to evaluate the health effects of MAR systems since there are many observed and unobserved household and community-level and hydrogeological confounders that may influence blood pressure.

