The study has several limitations. We will be unable to control salinity level of drinking water across the 16 MAR communities due to different hydrogeological conditions and volume of infiltrated water across the aquifers. Although the initial electrical conductivity of MAR water will be <2000 μS/cm, electrical conductivity is likely to vary across different MAR communities with the intensification of dry season. Therefore, MAR water salinity will differ across communities at a single point of time, and also for the same community at different points of time. This will result in different versions of exposures (ie, access to MAR water with different salinity levels) that may affect different responses for some participants depending on the version of exposure they will receive.^92 93^ To account this, we will specify the versions of exposure by measuring the salinity level of MAR water available in participants’ households and interpret the response as unit change of salinity at different MAR water salinity levels. As compliance of drinking MAR water may be different across communities despite active encouragement by promoters, one problem of the intention-to-treat analysis is that if the proportions of participants who will always drink MAR water are low compared with those who will not, the potentially greater effect of MAR intervention on blood pressure of fully participating individuals may be washed out by the smaller effect of those who will not comply. To account for this, as a secondary analysis, we will conduct ‘instrumental variable’ (IV) analyses by jointly running two regression models: a regression model for predicting urinary sodium excretion by drinking water salinity, and a regression model for blood pressure prediction given the urinary sodium excretion. The assumption of IV analyses is fulfilled in our context as the exogenous variable (IV) can only affect outcome variable (blood pressure) through influencing the endogenous variable (urinary sodium excretion).^94^ If MAR water has lower salinity than other water sources and if participants always drink MAR water, their urinary sodium excretion will be low compared with those who will not fully participate.

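### Handover order is drawn with no stated balance on district or site conductivity; a constrained draw would be a cheap improvement

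*Protocol article*

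**What the plan says.** - **Allocation.** Under Randomisation and intervention delivery: "We will randomly select four MAR communities to drink MAR water in each step following the first (baseline) step", done "by computer-generated random numbers". It takes place before the study starts, and "Randomisation will be conducted by an investigator who will not be directly involved in implementation of the stepped-wedge study". No stratification, matching or constraint is mentioned.
- **Size.** Under Sample size: "16 MAR communities will be required for the study with four communities randomised to access MAR water in each step".
- **Sites.** Under Study settings: "The study will be conducted at the community level in three districts in southwest coastal Bangladesh". The number of study communities per district is not given. A site must show "electrical conductivity (a measure of salinity) of water below 2000" μS/cm, which sets only an upper limit.
- **Model.** Under Statistical methods, the primary analysis has random effects for community, household and participant and fixed effects for visit, with adjustment for personal and socioeconomic factors. The visit effects are common to all communities, and no term lets a type of community have its own time course.
- **Seasonality.** The Sample size section says that the salinity problem and MAR water quality may change as the dry season advances, and that blood pressure may respond differently to different sodium levels. The Discussion names community-level and hydrogeological confounders that may influence blood pressure.

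**The concern.** In a stepped wedge, access is tied to calendar time. Common visit effects remove a seasonal trend that all communities share, and the community effect removes most of a constant level difference. Neither removes a trend that differs between types of community, for example if blood pressure climbs faster over the dry season in one district. With 16 clusters and four per step, one simple draw can easily place the types unevenly over the handover order, and part of the trend difference then enters the estimated access effect. The protocol's own remarks on seasonality and hydrogeology make such a difference plausible, though they do not show it.

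**Working it through.** **1. The plan's own figures.** Inputs from Sample size: effect 3, SD 20, 80% power, 5% type I error, design effect 3.04, 10% loss, 60 per cluster, five visits.

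- Per arm: 2 × (1.96 + 0.8416)² × 20² / 3² = 697.7, so 698. Two arms: 1396, as stated.
- Design effect over five visits: 5 × [(1 + 299ρ)/(1 + 179ρ)] × 0.4(1 − ρ). At ρ = 0.03 this is 3.036; it equals 3.04 at ρ of about 0.032 or 0.055. The article does not state ρ, so 0.01 to 0.05 is used below.
- 1396 × 3.04 = 4244; 4244 / 0.9 = 4715; 4715 / (60 × 5) = 15.7, so 16 communities. This reproduces.

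**2. How uneven a simple draw can be.** Assume two types of community, eight of each.

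- Six or more of one type in the first two (or the last two) handovers: 2 × (784 + 64 + 1) / 12,870 = 13.2%.
- At least one step made up of a single type: 3,126 / 12,870 = 24.3%.

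For districts, with an assumed 6/5/5 split, only about 12% of draws spread every district as evenly as possible over the four steps. With 8/4/4 it is about 2%.

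**3. What this does to the estimate.** Let the trend of one type depart linearly from the other, reaching D mm Hg at the fifth visit. In the generalised least squares estimator of the access effect (cluster-period means, 60 per cluster, SD 20), a community handed over at step s carries a net weight w(s) on that trend. The shift for a given draw is D × Σw(s) over the communities of that type.

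At ICC 0.03 with no participant correlation, w = −0.0081, 0.0234, 0.0158, −0.0310 for the first to fourth handover (sum about 0).

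- Σw² over 16 communities = 4 × 0.001824 = 0.00730.
- SD of the shift over random draws = D × √(16 × ¼ × 0.00730/15) = 0.0441 × D.

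| Assumed D (mm Hg) | SD of shift, ICC 0.03 | 95th percentile of absolute shift, ICC 0.03 | SD of shift, ICC 0.01 |
|---|---|---|---|
| 3 | 0.13 | 0.26 | 0.17 |
| 5 | 0.22 | 0.43 | 0.28 |
| 7 | 0.31 | 0.60 | 0.39 |

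At ICC 0.05 the SDs are 0.13, 0.21 and 0.30. They are almost the same if 60% of the within-cluster variance is persistent between participants. The mean shift over draws is 0. With two of each type in every step, the shift is 2D × (sum of the four w) = 0.

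**4. Against the sampling error.** The standard error of the access effect is 0.97 to 1.01 without participant correlation (ICC 0.01 to 0.05) and about 0.65 with the 60% assumption. For D = 7:

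- √(1.006² + 0.309²) = 1.052, an increase of 4.6%.
- √(0.65² + 0.298²) = 0.715, an increase of 10%.

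For D = 3 the increases are about 0.9% and 2%.

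**5. District version.** A trend difference of 1 mm Hg per month in one district (assumed, ICC 0.03) gives an SD of shift of about 0.17. Spreading districts evenly brings it to 0.10 (6/5/5) or 0 (8/4/4).

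**6. Constant differences.** A constant 5 mm Hg difference in one district moves the estimate by an SD of only 0.11 to 0.18 at ICC 0.03 to 0.05, and 0.04 to 0.06 with the 60% assumption. It is about 0.4 at ICC 0.01 without participant correlation. The model deals with most of this.

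**The case against.** The stated method is valid: computer-generated order, set before the study by someone outside implementation. Averaged over draws the shift is zero. The article is condensed, and a constraint on the draw may stand in the full protocol. All of this is accepted, and it is why the point is an improvement and not a fault.

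The trend sizes are assumed, and the documents report no blood pressure trend that differs by site. The Background gives one regional seasonal pattern, which common visit effects absorb. For scale, it also cites a difference between extreme sodium quintiles of 126.7 − 119.4 = 7.3 mm Hg, so D = 7 would need nearly that whole gap to open between two halves of the sites within five visits. The upper scenario is therefore extreme. The zero error under balance also holds by construction, because the trend is assumed to depend only on the balancing factor.

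Two stronger readings are tempting and are not supported:

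- **That the pilot showed the 16 trial sites to be unlike each other.** The Discussion does say "We identified unequal distributions of several important observed confounders across the communities such as socioeconomic status, and household characteristics". But the pilot covered four communities, two of them without MAR, and none of its results describes the 16 trial sites. Its finding that electricity supply predicted MAR is a contrast of MAR with non-MAR villages. All 16 trial sites have MAR, so it says nothing about handover order.
- **That the acknowledged salinity variation proves the mechanism.** "MAR water salinity will differ across communities at a single point of time, and also for the same community at different points of time" concerns the water offered after handover. That is variation in the treatment, not a blood pressure trend that runs regardless of access.

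**Conclusion.** The point holds as a low-cost refinement. The allocation is restricted only to four communities per step, the model has a single set of visit effects, and differing seasonal trends are then left to chance. The added error SD is about 0.13 to 0.3 mm Hg for an assumed 8/8 split and an assumed divergence of 3 to 7 mm Hg (up to 0.39 at ICC 0.01). This compares with a standard error of about 0.65 to 1.0 and a target of 3 mm Hg. A reader might infer that the effect estimate is biased or the randomisation unsound; neither follows. The size rests on assumed splits, trends, ICC and participant correlation, none of which the article gives.

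**What to change.** **If the draw is still open:** use constrained randomisation so that each step's four communities are spread as evenly as possible over the three districts and, where feasible, over high and low site conductivity from the site-selection readings. Adjust for the balancing factor in the primary model. District comes first: it is known before the draw and needs no measurement. The selection reading shows that the MAR system has lowered salinity, so it is only an indirect marker of what households drink before access; household water is measured at study visits, after the draw. With uneven district numbers, exact balance on both factors may not be possible, so the constraint should be stated as a tolerance.

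**If the draw is already made,** as the synchronised handover schedule suggests it may be: leave it, report whether it was constrained, and prespecify a sensitivity analysis with a district-by-visit term or a term for baseline household water salinity by visit. Forcing such an interaction into the primary model is debatable with 16 clusters.

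**Cost:** a few lines of randomisation code, slightly more travel in each handover month, and some degrees of freedom: two for a district main effect, and (3 − 1) × (5 − 1) = 8 for district by visit in the sensitivity analysis. The sample size does not change.
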